### Sample size

The sample size was informed by the faecal 16S rRNA gene amplicon datasets generated for the proof-of-concept study of 12 to 18-month-old Bangladeshi children with MAM.^11^ In that study, we identified 209 bacterial Amplicon Sequence Variants (ASVs) that were present above 5 counts in at least 5% of the 939 faecal samples analyzed from 118 participants. We calculated 95% confidence intervals (CI; mean ± 1.96 standard error) for the change (delta) in abundance of each of the 209 ASVs between day 0 (pre-intervention) and 4 weeks of intervention for the 59 children in the MDCF-2 treatment group of the POC study. Using a bootstrapping approach with ASV data from 5000 subsets of 20 children from the MDCF-2 group and 5000 subsets of 20 children from the RUSF group, we identified 121 ASVs whose mean changes in abundance for the MDCF-2 subsets fell within the 95% CI of the mean changes for the 59 MDCF-2 participants, but not in children who had received RUSF, with 80% power (“MDCF-2-responsive ASVs”). Therefore, each arm will include a minimum of 20 children who complete the study. Considering potential drop-outs (15%), 23 children will be recruited per arm.

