### Analysis plan

To assess the comparability of microbiota repair elicited by shelf-stable test formulations of MDCF-2 and the reference kitchen prepared formulation, we will sequence PCR amplicons generated from variable region 4 of bacterial 16S rRNA genes present in DNA isolated from faecal samples collected from participants in the different study arms immediately prior to intervention (day 0) and at the end of intervention (day 28). ASV data will be processed using DADA2 [15] and filtered as described [10]. We will calculate 95% confidence intervals of the mean change in abundance of each of the MDCF-2-responsive ASVs identified in this study, between day 0 and day 28, in children who received the reference MDCF-2 formulation, as well as the mean change in abundance for each of these ASVs in participants receiving the test formulations. A test formulation will be considered equivalent to the reference MDCF-2 if >70% of the MDCF-2-responsive ASVs have mean changes in abundance in children consuming a test formulation between day 0 and day 28 that fall within the 95% CI of their mean changes in abundance in the reference MDCF-2 arm. Another embodiment of the analysis of microbial community repair elicited by the reference MDCF-2 and test formulations will involve a comparison of their effects after 28 days of treatment on the abundances of metagenome-assembled genomes (MAGs) identified by shotgun sequencing of the same faecal DNA samples used to produce 16S rDNA amplicons.

Exploratory outcomes will include the effects of the test formulations on features of the plasma and faecal proteomes, including MDCF-2-responsive proteins that are associated with various facets of healthy growth using approaches described in the MDCF-2 POC study [10].

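### The Sample size and Analysis plan sections disagree on which ASVs the >70% equivalence rule counts, and read literally the list and its benchmark could come from the same reference children

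*Protocol article*

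**What the plan says.** Protocol article, Sample size. The term is defined on POC data, in children aged 12 to 18 months: "we identified 121 ASVs whose mean changes in abundance for the MDCF-2 subsets" lay inside the interval for all 59 MDCF-2 children, "but not in children who had received RUSF, with 80% power (“MDCF-2-responsive ASVs". The candidate pool was 209 ASVs, and the interval is given as "95% confidence intervals (CI; mean ± 1.96 standard error". This section refers to the POC as that study.

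Protocol article, Analysis plan. The interval is to be calculated for the "mean change in abundance of each of the MDCF-2-responsive ASVs identified in this study, between day 0 and day 28", in this trial's reference arm. The criterion follows: "A test formulation will be considered equivalent to the reference MDCF-2 if >70% of the MDCF-2-responsive ASVs have mean changes in abundance" that "fall within the 95% CI of their mean changes in abundance in the reference MDCF-2 arm". The section gives no rule for identifying responsive ASVs in this trial. It also does not say that the 121 are meant.

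**The concern.** The membership of the list is part of the primary criterion. It sets the denominator of the 70% and decides which changes count. Two sections of the same article describe it differently, so two analysts could score different endpoints.

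The literal reading of the Analysis plan adds a statistical problem. If an ASV enters the list because it moved in the reference arm, its observed reference change is on average too large (winner's curse). The test arms carry no such selection, so their means tend to fall back towards the true value and out of the interval. A food that works exactly as well as kitchen-prepared MDCF-2 could then be judged not equivalent, and every test formulation would face the same distorted benchmark. What is at stake is wrongly discarding a usable shelf-stable product.

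**Working it through.** **The plan's own figures.** Recruitment: 20 × 1.15 = 23 per arm, as stated. The 80% power figure cannot be recomputed without the ASV data, but a normal approximation brackets it. The chance that the mean of a 20-child subset lies in the 59-child interval is
- drawn with replacement: P(|Z| < 1.96·√(20/59)) = P(|Z| < 1.141) = 74.6%;
- drawn without replacement: P(|Z| < (1.96/√59)/√(1/20 − 1/59)) = P(|Z| < 1.404) = 84.0%.

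**List fixed beforehand.** Take 20 children per arm and a test food identical to the reference. In standard-error (SE) units the two arm means differ by a normal variable with SD √2. The chance that one ASV falls inside is P(|Z| < 1.96/√2) = 83.4%, whatever the true change. More than 70% of 121 means at least 85 (0.70 × 121 = 84.7). With independent ASVs the binomial probability of passing is 0.9999. With an assumed correlation of 0.2 it is about 0.95.

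**List chosen on the same reference children.** Three selection rules were simulated; all three are assumptions:
- A: the reference change is significant (|z| > 1.96);
- B: the reference differs significantly from RUSF;
- C: the RUSF mean lies outside the reference interval, the nearest single-sample analogue of the rule in Sample size.

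True changes are normal around 0 with SD τ in SE units. Dividing by √20 gives units of the between-child SD. RUSF has no effect, there are 209 candidate ASVs, and each cell rests on 3000 simulated trials for the pass rate.

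| τ (SE) | in SD | Share inside, A / B / C | Trial passes >70%, A / B / C (independent ASVs) | Same, correlation 0.2 |
|---|---|---|---|---|
| 0.5 | 0.11 | 51.5 / 64.1 / 72.1% | 7 / 33 / 61% | 15 / 40 / 65% |
| 1 | 0.22 | 69.5 / 71.9 / 76.8% | 49 / 58 / 87% | 59 / 62 / 82% |
| 2 | 0.45 | 80.7 / 80.1 / 81.5% | 99 / 96 / 99.5% | 91 / 89 / 91% |
| 3 | 0.67 | 82.6 / 82.3 / 82.7% | >99% for all | 94 / 93 / 94% |

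At a spread of exactly 0.2 SD (0.2·√20 = 0.89 SE) the expected share is 67% under A. Under B it is 70% if RUSF has no effect and 75% if RUSF effects are independent with the same spread. Under C it is 76% and 79% respectively. At a spread of 0.1 SD rule A gives about 49%; at 0.3 SD it gives 76%.

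For a single fixed true change, rule A gives 64% at 0.2 SD, 74% at 0.3, 82% at 0.4 and 85% at 0.5. The reference change is overstated about 2.7 to 2.8 times at 0.2 SD and 1.9 times at 0.3 SD.

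**The case against.** The strongest reply is that no list is re-derived in this trial. Sample size formally defines the term as the 121 POC ASVs, the Analysis plan reuses it, and no new identification rule is given. Sample size also uses the verb for plain detection: "In that study, we identified 209 bacterial Amplicon Sequence Variants (ASVs" present above a count threshold. The disputed phrase could therefore mean those of the 121 that are detected in these samples after filtering. On that reading selection took place in other children and the bias disappears. This stands as a possible reading, but not as the only one: the article calls the POC that study and the current trial this study, so the literal sense points the other way. On either reading the sentence needs correcting.

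Second, the larger losses come from rule A, which the article does not contain. Under rule C, the closest to its own rule, the share stays above 70% at an SD of 0.2, and an identical food usually passes. This also stands. Even so, the pass rate under C drops to 61% to 87% (independent ASVs) when signals are weak.

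Third, the bias works against declaring equivalence, so by this mechanism it costs power and does not create false equivalence. That is correct and limits the harm.

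A reader might also infer that the list stays open until unblinding, or that the endpoint is chosen after the data are known. The article does not say when the list is fixed, and a condensed article may leave that to the analysis plan, so neither inference is supported.

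**Conclusion.** The conflict between the two sections is established, and it lies inside the primary decision rule. The circularity is conditional: it follows from the literal wording of the Analysis plan, but the article does not establish that the list will be derived from this trial's reference children.

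If it is so derived, the expected share for an identical food falls from 83% to between about 49% and 82% for true changes spread with SD 0.1 to 0.5. Around 0.2 SD the result sits on either side of the 70% bar depending on the rule; at a true change of about 0.5 SD the effect is negligible. These figures rest on normal approximations, 20 completers per arm, and assumed selection rules and effect sizes. It would be wrong to conclude that an identical product will fail: it can fail when responses are weak relative to the SE. If the 121 POC ASVs are meant, the defect is one of wording alone.

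**What to change.** In the Analysis plan, replace the qualifier that places identification in this study with a named list, fixed before unblinding and independent of the reference-arm data that supply the interval. The 121 POC ASVs are the obvious candidate. Because these children are 8 to 12 months old and the POC children were 12 to 18 months, drop only ASVs that fail a prevalence filter applied to pooled, arm-blinded data, and apply the 70% to those retained. Report ASVs newly identified here as exploratory. Identifying ASVs in data separate from the data behind the benchmark interval would also remove the circularity.

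The cost is a change of wording and the filing of a list, with no change to sample size or conduct. The downside is that taxa responsive only in 8-to-12-month-olds stay exploratory.

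### The share-of-ASVs equivalence rule compares a test-arm point estimate with the reference arm's own confidence interval, so its false-equivalence rate is uncontrolled

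*Protocol article*

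**What the plan says.** The operational rule for the primary outcome is in the protocol article, Analysis plan: "A test formulation will be considered equivalent to the reference MDCF-2 if >70% of the MDCF-2-responsive ASVs have mean changes in abundance" between day 0 and day 28 "that fall within the 95% CI of their mean changes in abundance in the reference MDCF-2 arm". For the test arms, the section calculates only point estimates: "as well as the mean change in abundance for each of these ASVs in participants receiving the test formulations". The ASVs concerned are "each of the MDCF-2-responsive ASVs identified in this study". No condition is stated that the reference-arm change must differ from zero, and the RUSF arm has no part in the decision.

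The Sample size section gives the interval as "CI; mean ± 1.96 standard error" and sets a minimum of 20 completers per arm. Its power statement describes how ASVs were chosen in the POC data: "we identified 121 ASVs whose mean changes in abundance for the MDCF-2 subsets fell within the 95% CI" of the 59 MDCF-2 children, "but not in children who had received RUSF, with 80% power". The Outcome measures section describes equivalence as the absence of a statistically significant difference, which supplies no margin either.

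**The concern.** An equivalence claim needs a margin fixed in advance and an interval for the difference that carries the error of both arms. This rule has neither. The acceptance region for each ASV is as wide as the reference arm is imprecise, so imprecision is rewarded, and losing reference-arm children moves the result towards equivalence. The article ties the 70% cut-off to no probability of passing, either for an identical food or for an inactive one. The result selects the formulation that goes into larger, longer studies with growth outcomes, so a false pass would carry an inactive product forward.

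**Working it through.** **Inputs from the article.** 20 completers per arm; interval of mean ± 1.96 SE (stated under Sample size, assumed to carry over to the Analysis plan); cut-off >70%. With the 121 ASVs of the POC list, 0.70 × 121 = 84.7, so at least 85 must lie inside.

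**Assumed, because the article gives no values.** Normally distributed means, equal SDs unless stated, a range of effect sizes, and independent ASVs unless stated.

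**Formula.** Let d be the true test-minus-reference difference in SD units, n_r and n_t the arm sizes, h = 1.96/√n_r and s = √(1/n_r + 1/n_t). Then

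P(inside) = Φ((h − d)/s) − Φ((−h − d)/s).

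**1. Test-arm error.** With n_r = n_t = 20, h = 0.438 and s = 0.316. For d = 0, P = 2Φ(1.386) − 1 = 0.834. An identical food therefore has 83% of ASVs inside on average, not 95%. The SD cancels, so this needs no outside figure.

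**2. Tolerance of a real shift.** At 20 per arm:

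| d on every ASV (SD) | Expected share inside | P(≥85 of 121), independent ASVs |
|---|---|---|
| 0 | 83% | >99% |
| 0.20 | 75% | 91% |
| 0.25 | 71% | 61% |
| 0.26 | 70% | 52% |
| 0.30 | 66% | 18% |
| 0.40 | 54% | <0.1% |

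With correlation 0.3 between ASVs (one common factor, simulated), the pass rate is 68% at d = 0.20, 46% at 0.30 and 29% at 0.40.

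**3. Noise helps.** Hold the true difference at 0.5 units and the test-arm SD at 1. As the reference-arm SD goes from 0.5 to 1, 1.5 and 2, the expected share inside goes from 13% to 42%, 65% and 77%. For arm size, take d = 0.4 SD and 20 test children: the share is 51% with 23 reference children, 54% with 20 and 62% with 15.

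**4. A food with no effect.** Let the reference food's true standardised changes vary across ASVs with mean 0 and SD τ, and let the test food's be zero. The expected share inside is 2Φ(0.438/√(τ² + 0.1)) − 1. Pass rates come from simulation with SDs estimated from 20 children per arm and 121 independent ASVs:

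| τ | Expected share inside (known SD) | Simulated pass rate |
|---|---|---|
| 0.20 | 76% | 88% |
| 0.25 | 72% | about 60% |
| 0.30 | 69% | about 28% |
| 0.40 | 61% | about 1% |

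At τ = 0.30, the pass rate is about 13% with 23 reference children, 28% with 20 and 66% with 15.

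**5. What the POC selection implies.** If each selected ASV has RUSF subset means outside the 59-child interval 80% of the time, the implied RUSF difference is about 0.41 to 0.44 SD. Against a 20-child reference interval that gives an expected 49% to 53% of ASVs inside.

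**6. The stated 80% power.** It refers to "fell within the 95% CI of the mean changes for the 59 MDCF-2 participants", an interval about √(59/20) = 1.7 times narrower than one from 20 children at the same SD. It cannot be transferred to the trial rule.

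**The case against.** The strongest reply is that the no-effect pass rates rest on assumed effect sizes, and that the one anchor in the article points the other way: under step 5 a RUSF-like food falls well short of 70%. This stands, with limits. It assumes that the POC list and effects from children aged 12 to 18 months hold at 8 to 12 months. Strong positive correlation with differences all in one direction would still let some such foods pass (18% to 25% at correlation 0.3). If the responsive ASVs had to show a reference interval excluding zero, simulated pass rates for an inert food would be 0% to 19%, but the article states no such condition.

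A reader might also infer that the rule would fail an identical product. The formula does give an expected share of only 68% for a reference arm of 59 and 58% for one of 100, but the Sample size section plans 23 recruited and at least 20 completing per arm, so those sizes cannot occur. At 20 per arm an identical food passes in over 99% of trials with independent ASVs and about 91% at correlation 0.3.

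The effect of dropout is modest in some settings: at d = 0.4 SD, 15 reference children still leave the expected share below 70%. Finally, an unseen analysis plan may report operating characteristics. That would not alter the structure of the rule, which the article fixes.

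**Conclusion.** The concern holds. The rule ignores test-arm error and replaces a margin with a region set by reference-arm noise. Both follow from its wording. At 20 per arm it tolerates a shift of about 0.26 SD on every ASV before the expected share drops to 70%, given normality and equal SDs.

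The false-equivalence rate is uncontrolled, which is not the same as known to be high. Across the assumed range, a no-effect food passes in anything from about 88% to about 1% of trials. It would be tempting to conclude that the trial will probably pass an inactive food. The article does not support that, because it gives no effect sizes, SDs or correlations, and its POC selection suggests that a RUSF-like food would usually fail. What is missing is any step in the rule that secures this protection.

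**What to change.** 1. Before unblinding, calibrate the share cut-off by resampling the POC data. Use two disjoint groups of 20 MDCF-2 children as reference and test, and 20 RUSF children as an alternative test group. Repeat the ASV selection in children held out from the evaluation; otherwise the RUSF pass rate will look too low, because the same children chose the ASVs.
2. Choose the cut-off so that P(pass | RUSF) is at most 5%, and state P(pass | MDCF-2).
3. Apply the same rule to this trial's RUSF arm, and claim equivalence for a test food only if RUSF fails it.
4. Report the two-sample CI of the test-minus-reference difference for each ASV as supporting precision, not as a fixed-margin test. At 20 per arm the 90% CI half-width is about 1.645 × √(2/20) = 0.52 SD. Two one-sided 5% tests with 80% power at no true difference need a margin of about (1.645 + 1.282) × √(2/20) = 0.93 SD.

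**Cost.** Re-analysis of data that the sponsor holds and revised wording of the rule; no extra children or visits. Holding out is tight: 59 − 40 = 19 MDCF-2 children remain for selection in any one split, so selection will be noisier than in the POC study and should be repeated over many splits. The chance of declaring equivalence may fall.

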### Current status of enrolment

Enrolment for the study began on 31 October 2021. We are currently recruiting study participants. The enrolment is expected to be completed by 31 December 2022.

### Data confidentiality and archiving

Privacy, anonymity and confidentiality of data will be strictly maintained. All trial related information will be kept confidential and stored securely at the central office in icddr,b. Codes will be used to depersonalise the data. The linking code, electronic data files and paper forms are stored in a separate location under password protections or lock and key. Access to the data will be restricted to the investigators.

## Discussion

The current version of MDCF-2 is freshly prepared in local kitchens on a daily basis and distributed locally on the same day without sterilization. Given the need to identify a bioequivalent formulation that can be produced at scale and distributed to other geographic locales, we have designed this study of children with MAM to test alternative shelf-stable prototypes of MDCF-2 that each provide ~250 kcal/day, plus 70% RDA of key micronutrients. Outcomes will include the organoleptic acceptability of the prototypes and their effects on microbiota repair over 4-weeks of intervention. Our goal is to identify a packaged, shelf-stable formulation for advancing into larger, longer proof-of-concept studies that evaluate efficacy using clinically-relevant growth outcomes. One weakness of this study is that it is not possible to attain full blinding since the test prototypes are not packaged in a similar manner.

In conclusion, this study aims to establish the acceptability of a scalable, shelf-stable formulation that is bioequivalent to MDCF-2 with respect to microbiota repair in 8-12-month-old Bangladeshi children with moderate acute malnutrition. The results of this study will inform the selection of a shelf-stable formulation of its efficacy for treating of moderate acute malnutrition.

## Data Availability

All data related to this study protocol are within the manuscript and its supporting information files. Additional information is available from the corresponding author on reasonable request.

## Abbreviations

MAM: Moderate Acute Malnutrition
MDCF: Microbiota Directed Complementary Food
RUSF: Ready-to-Use-Supplementary Food
MUAC: Mid-Upper Arm Circumference
WHO: World Health Organization
DNA: Deoxyribonucleic Acid
ASV: Amplicon Sequence Variant
